**Methods::**

Sixty subjects of both sexes between 18 and 60 years (30 volunteers with clinically stable bronchiectasis and 30 healthy volunteers) will be included. Participants with chronic obstructive pulmonary disease, decompensated cardiovascular or metabolic diseases, neuromuscular and musculoskeletal diseases, and active smokers will be excluded. Volunteers will be randomly allocated to the pulmonary rehabilitation or control groups. The primary outcomes will be nasal transport time as evaluated by nasal saccharin transport time, analysis of nasal lavage, enzyme immunoassay of exhaled expiration, and analysis of the mucus properties. The secondary outcomes will include pulmonary function tests, impulse oscillometry, heart rate variability analysis, and quality of life questionnaires.

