##### Secretion analysis

2.6.1.2

Mucus samples will be collected by voluntary coughing and expectoration into a glass. The mucus will be separated from the saliva and then evaluated in terms of its adhesiveness and purulence. After this initial evaluation, the respiratory secretions will be placed in plastic tubes and covered with mineral oil to prevent dehydration, followed by freezing for subsequent analysis.^[25]^ The evaluated parameters will be the surface properties, appearance, relative transport velocity on a frog palate, transport measured in a simulated cough machine, and the contact angle.^[26]^

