##### Cytokine analysis

2.6.1.6

The concentrations of tumor necrosis factor-alpha, interleukins 6 and 10 in nasal lavage fluid samples will be determined using high-sensitivity immunoassay (ELISA) performed according to the instructions of the supplier of the kit.

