### Sample size calculation

2.7

The sample calculation was performed based on the mucociliary clearance evaluated by the saccharine transport time.^[39]^ The detected effect should have an average of 4 minutes with a standard deviation of 3 minutes, alpha of 5%, and power of 95%. The results indicate that 60 volunteers would be needed with 15 in each subgroup.

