### Statistical analysis

2.8

A biostatistician will analyze the data in a blinded manner. The normality of the data will be verified by the Shapiro–Wilk test. For comparing the values between 2 groups, the Student *t* test will be used for parametric variables and the Wilcoxon test will be used for nonparametric variables. Analysis of variance will be used for comparison between 3 or more groups, followed by a multiple comparisons test when indicated for parametric data or the Kruskal–Wallis test for nonparametric data. Data correlation will be assessed using the Pearson or Spearman correlation test for normal and nonnormal distributions, respectively. The level of significance will be set at 5%. Statistical analysis will be performed through the R version 3 (2013-05-16) (The R Foundation for Statistical Computing, Vienna, Austria) and SAS version 9.2 (Cary, NC).

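### About 13 unranked variables are called primary under a single 5% level with no control across outcomes, while the stated power covers saccharin transport time alone

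*Protocol article*

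**What the plan says.** **Body, sections 2.6.1.1 to 2.6.1.6.** Six headings stand under the primary outcomes: saccharin transport time, secretion analysis, nasal lavage fluid, exhaled breath condensate with pH, nasal exhaled nitric oxide, and cytokine analysis. Most of the variables come from the secretion section. It starts with a first look at adhesiveness and purulence and then continues: "The evaluated parameters will be the surface properties, appearance, relative transport velocity on a frog palate, transport measured in a simulated cough machine", with contact angle as the last item. Section 2.6.1.6 states that TNF-alpha, IL-6 and IL-10 "in nasal lavage fluid samples will be determined using high-sensitivity immunoassay (ELISA". Section 2.6.1.4 also stores condensate for cytokine measurement but does not say which cytokines.

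**Abstract, Methods.** The list is shorter: "The primary outcomes will be nasal transport time as evaluated by nasal saccharin transport time, analysis of nasal lavage, enzyme immunoassay of exhaled expiration", plus mucus properties. That makes four items.

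**Section 2.7.** "The sample calculation was performed based on the mucociliary clearance evaluated by the saccharine transport time". The inputs are a 4-minute effect, a standard deviation of 3 minutes, alpha 5% and power 95%, giving 15 per subgroup and 60 in total.

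**Section 2.8.** For two groups, "the Student *t* test will be used for parametric variables and the Wilcoxon test will be used for nonparametric variables". For three or more groups, analysis of variance is "followed by a multiple comparisons test when indicated for parametric data". The error rate is given once: "The level of significance will be set at 5" per cent.

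**Section 2.3.** Assessments are at the start, week 8 and week 12. None is named as the primary time point.

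**The concern.** A 5% level describes the trial's main claim only if there is one main test, or a rule that ties several together. Here the article gives the same primary status to every variable in section 2.6.1 and supplies no such rule. As written, a difference in any one of them could be reported as a positive primary result. The reader would have no way of knowing that it was one of about a dozen chances.

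The 95% power has the matching weakness. It was computed for saccharin time at an unadjusted 5% and says nothing about the other primary variables.

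The list also matters beyond testing. Section 2.3 says that data from a discontinuation visit will be used for the primary outcomes, so which variables count as primary also affects data handling. The abstract and body do not give the same answer.

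**Working it through.** **1. Reproduce the plan's own figure (section 2.7).** Reading the effect as a difference between two equal subgroups, tested two-sided (sidedness is not stated):

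n per group = 2 × [SD × (z for 0.975 + z for 0.95) / difference]² = 2 × [3 × (1.960 + 1.645) / 4]² = 14.62, rounded up to 15. Four subgroups give 60.

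The stated figure reproduces for one unadjusted test of saccharin time. An exact t calculation gives 94.1% power at 15 per group and would need 16, which is a trivial difference.

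**2. Count the primary variables (section 2.6.1).**

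| Section | Variables | Count |
|---|---|---|
| 2.6.1.1 | saccharin time | 1 |
| 2.6.1.2 | adhesiveness, purulence | 2 |
| 2.6.1.2 | surface properties, appearance, frog-palate velocity, cough-machine transport, contact angle | 5 |
| 2.6.1.3 | source sample for the cytokines, not counted again | 0 |
| 2.6.1.4 | condensate pH | 1 |
| 2.6.1.5 | nasal nitric oxide | 1 |
| 2.6.1.6 | TNF-alpha, IL-6, IL-10 in nasal lavage | 3 |
| **Total** | | **13** |

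Leaving out adhesiveness and purulence gives 13 − 2 = 11. Adding three condensate cytokines (an assumption, since none is named) gives 13 + 3 = 16.

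**3. Chance of at least one false positive.** Assume that all nulls are true and that each variable gets one two-sided 5% test.

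For k independent tests the chance is 1 − 0.95^k. For k = 13: 1 − 0.513 = 48.7%. For k = 4: 1 − 0.8145 = 18.5%.

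For a common correlation r between the test statistics, it is 1 − E{[Φ((c − √r·U)/√(1−r)) − Φ((−c − √r·U)/√(1−r))]^k}, with U standard normal and c = 1.96, integrated numerically. The documents give no correlations, so r is varied:

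| Variables | r = 0 | r = 0.5 | r = 0.7 | r = 0.8 |
|---|---|---|---|---|
| 4 (abstract items) | 18.5% | 15.6% | 13.0% | 11.4% |
| 11 | 43.1% | 30.4% | 22.3% | 18.0% |
| 13 | 48.7% | 33.4% | 24.1% | 19.2% |
| 16 | 56.0% | 37.4% | 26.4% | 20.7% |

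Every cell is more than twice the stated 5%.

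**4. What equal adjustment would do to the stated power.** Bonferroni over 13 variables gives alpha = 0.05/13 = 0.00385. With 15 per subgroup, power for the saccharin effect falls to 78% (69% by exact t). Restoring 95% by the same normal formula takes 24 per subgroup, or 4 × 24 = 96 in total.

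**5. Compare the lists.**

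| Item | Abstract | Section 2.6.1 |
|---|---|---|
| Saccharin time | primary | primary |
| Mucus properties | primary | primary |
| Nasal lavage | primary | primary, three analytes named |
| Immunoassay of exhaled sample | primary | condensate cytokines planned, analytes not named |
| Condensate pH | not listed | primary |
| Nasal nitric oxide | not listed | primary |

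**The case against.** **The analysis plan may settle it.** Section 2.8 is silent on adjustment across outcomes and does not rule it out. That is fair, and the missing adjustment is not in itself the fault. But the choice of primary outcomes is made in this document, and it is made without a ranking. Splitting alpha equally later would undo the stated power (step 4). A fixed sequence starting with saccharin time would keep both alpha and power, but it needs the order that the protocol does not give. A rule that all primaries must succeed would avoid the inflation, but no such rule is stated and the 95% power would not apply to it.

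**The lead outcome is discernible.** Saccharin time comes first in both lists and alone is powered. This stands, and it is why the remedy is easy. Nothing declares it the lead, however.

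**The count is a reading.** This also stands, hence the range of 11 to 16. Six headings are not six outcomes either, because the lavage section describes the sample that the cytokine section assays.

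Three stronger readings are tempting, and the document does not support them:

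- A reader might double the number of tests for weeks 8 and 12. Section 2.8 states no visit-by-visit testing, and two values of one variable in the same person are not independent.
- A reader might infer that the abstract's exhaled immunoassay contradicts a body that assays nasal lavage only. Section 2.6.1.4 does plan condensate cytokines; only the analytes are missing.
- A reader might infer that participants without lung disease cannot supply mucus, so secretion outcomes cannot be primary for all 60. The document does not say so, and this is a feasibility question separate from error control.

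**Conclusion.** The point holds in this form: the 5% error rate and 95% power do not describe the primary set that section 2.6.1 fixes. For 13 variables the chance of at least one false-positive primary result is 49% if they are independent, about 33% at correlation 0.5 and 24% at 0.7. Even the abstract's shorter list gives 18.5% under independence. These figures assume true nulls throughout, one test per variable and correlations that the document does not give; correlation above about 0.7 brings the 13-variable figure below 24%.

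The sample size is not wrong on its own inputs. It belongs to a design with one primary outcome, and the outcome list describes a different one. The differences between abstract and body are limited to nasal nitric oxide, condensate pH and the unnamed condensate analytes.

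**What to change.** - Name saccharin transport time as the single primary outcome, at one stated time point (for example week 12, the end of the programme) and for one stated comparison (for example exercise versus no exercise in participants with bronchiectasis), tested at two-sided 5%.
- Make the secretion properties, nasal-lavage cytokines, condensate measures and nasal nitric oxide secondary or exploratory, either with Holm adjustment or with an explicit statement that no confirmatory claim is made.
- Make the abstract and section 2.6.1 list the same outcomes, and name the condensate analytes.

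This is a change of wording in the protocol and the registry entry; section 2.9 already provides for telling the registry and the ethics committee of modifications. The total stays at 60, and the stated alpha and power then apply to the named comparison. The cost is that the demoted variables can no longer carry a confirmatory claim. Keeping all 13 as primaries with Bonferroni adjustment would instead need about 96 participants for the same power on saccharin time.

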### Data management

2.9

All data will be entered electronically. There will be a subject identification code list and each participant will receive a participant study identification number. Confidential documents will be retained in the institution's computer in the laboratory. A password system will be utilized to control access. Back up of data will be kept in locked cabinets. Any modifications to the protocol and administrative changes of the protocol will be communicated to ClinicalTrials.gov and Research Ethics Committee and clinical research unit of the Hospital das Clínicas da Faculdade de Medicina de Ribeirão Preto. All principal investigators will have access to the final trial dataset.

## Discussion

3

The main problem for bronchiectasis patients is the retention of secretions^[1]^ associated with bacterial colonization and inflammation, with frequent exacerbations by infection. These cycles can contribute to the progression of the disease. Patients with bronchiectasis present reduced exercise capacity associated with structural changes in lung tissue and progressive airflow obstruction. In the more advanced phases of the disease, patients can present static and dynamic hyperinflation, leading to a decrease in tidal volume along with increases in dead space ventilation and effort-related dyspnea.^[40–44]^ These factors lead to a sedentary lifestyle, which affects daily life activities and worsens quality of life.

International guidelines recommend pulmonary rehabilitation programs for these individuals to improve exercise capacity through the effects on aerobic capacity and peripheral musculature, as well as improving disease control and quality of life.^[45]^ There is little information about the effects of physical training on patients with bronchiectasis. However, it is likely that the benefits of physical training in these patients are at least comparable to those demonstrated in other clinical conditions with respiratory dysfunction.^[21,46,47]^ Prospective studies about the effects of pulmonary rehabilitation on bronchiectasis patients have shown improvements in exercise tolerance and quality of life in the short term.^[21,36,48]^ Improvements were observed in the exacerbation frequency and time of the first exacerbation in the long term.^[36]^ Retrospective studies have demonstrated positive effects on exercise capacity, quality of life, and pulmonary function.^[46,49]^

The benefits of exercise have been demonstrated for secretions clearance in other respiratory diseases,^[50]^ as well as for reductions in mucus viscosity and elasticity.^[51–54]^ In subjects with cystic fibrosis, greater mucus expectoration after exercise has been reported. This effect may be due to increased ventilation and respiratory flow. The same study also observed that exercise on a treadmill reduced the mechanical impedance of the mucus, probably due to trunk oscillations associated with walking.^[55]^

Regular physical training can modify the autonomic balance and may accelerate the physiological recovery of the vagal sympathetic interaction.^[56]^ The autonomic nervous system acts on mucociliary clearance. Patients subjected to lung transplantation present a reduction in mucociliary clearance due to denervation since the vagus nerve mediates the main components of the mucociliary clearance system, the frequency of ciliary beats, and mucus secretion.^[57,58]^

The present study could provide new information about the unclear mechanisms regarding exercise to aid in the removal of secretions. We expect to identify whether mucociliary transport dysfunctions occur through only the oscillations promoted by increased airflow and body movement during exercise, or whether there are other mechanisms related to pulmonary mechanics, inflammation, or the autonomic nervous system.
